#### Recruitment

Eligible occupational therapy students will be provided with information about the study and invited to participate at the beginning of, or just prior to, the start of the semester in which the trial is to be implemented. All students will be informed that (1) if enrolled in the unit they will undertake either the SCP or TCP as determined by random selection; (2) all students will complete the same instruments towards their assessment and provide feedback on their placement experience; and (3) only data from students who consent to participate will be included in the trial. Students will be told that taking part in the trial and allowing their data to be used is voluntary and that their experience and grades in the unit of study will not be affected should they choose not to participate. Prior experience suggests the recruitment rate of students (with efficient and focussed strategies) will achieve 85–90% of the student population. With multicentre trials, the rate is often less, perhaps 70%, although Watson et al. [22] found that, of 1200 eligible students for a study using simulation to replace clinical time, only 410 students volunteered to participate (34%). Therefore we estimate that a recruitment rate of 60% of eligible students will be achievable. In 2015, the participating universities estimated that 774 students would be eligible for inclusion in the trial in 2016, thus a sample of 425 (55% of the expected eligible sample) appears feasible.

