### Randomisation and allocation

Using a procedure specified by the national research team, the local research assistant at each site will recruit students to the trial, collect consent forms and allocate students to either the SCP or TCP group in a 1:1 ratio. A software package will be used to generate the random allocation sequence of students who have consented to submit their data for the trial. This software is freely available from the Internet (http://random-allocation-software.software.informer.com/2.0/) and is described in the literature [34]. The allocation is performed at each site by the local research assistant utilising block randomisation once student enrolment in the unit of study is determined.

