### Instruments and measures

Outcomes will be assessed using a variety of tools to gather both qualitative and quantitative data to address the research questions. Data will be collected immediately prior to or at the beginning of placement, on completion of placement and at the end of the unit of study (see Table 2). Demographic data including student age, gender, university, prior qualifications and prior placement experience will also be collected.

**Table 2 Tab2:** Description of the instruments used to collect data across the trial

Instrument	Type	Timing	Respondent
SPEF-R	Paper-based	Complete across placement week, finalising during morning of 5^th^ day of placement	Clinical supervisors
SPEF-R, self assessment	Paper-based	Complete across placement week, finalising during the 5^th^ day of placement	Students (self-report)
Pre-placement questionnaire	Paper-based	Pre-placement briefing 1 week prior to placement *Or* morning of 1^st^ day of placement	Students (self-report)
Post-placement questionnaire	Paper-based	Afternoon of 5^th^ day of placement	Students (self-report)
SPEF-R, student review	Paper-based	Complete across placement week, finalising during the afternoon of 5^th^ day of placement	Students
Examination	Paper-based	Within 4 weeks of placement conclusion	Students
Sessions evaluation	Online	Within 2 weeks of placement conclusion	SCP students only
Focus group feedback	Transcribed audio	Within 4 weeks of placement conclusion	Students Clinical educators
Clinical educator survey	Online	Within 2 weeks of placement conclusion	Clinical educators (clinical supervisors and simulation facilitators)
Cost data collection	Digital	Across the full extent of the trial	Partner university site coordinators, investigators, placement support staff and project support staff

*SPEF-R* Student Practice Evaluation Form-Revised

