#### Student confidence

Student confidence will be measured prior to placement and again at the end of placement using the Student Level of Confidence Questionnaire, developed specifically for occupational therapy students to complete in relation to their clinical placement experiences [33]. The questionnaire is a self-report measure including 41 items. Students rate their confidence from 1 (strongly disagree) to 5 (strongly agree), and scores are summed for a total score ranging from 41 to 205. The questionnaire has demonstrated high internal consistency (Chronbach’s alpha = .96), and principal component analysis, with oblique rotation, demonstrated the items formed one ‘confidence’ component scale [37]. According to the designers of the instrument, there is evidence that the tool is responsive to change in confidence levels both within a placement period (6 weeks duration tested in the study) and across placements (four placement periods).

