To evaluate whether students who experience an SCP report non-inferior levels of confidence during placement outcomes compared to those who experience a TCP, the difference between change scores on the confidence questionnaire between SCP and TCP groups will be assessed using an independent samples *t* test. Between-group analyses of mean total score differences on this questionnaire, both pre- and post-SCP and TCP, will be determined using independent samples *t* tests. Within-group differences will be established using paired samples *t* tests.

To assess students’, educators’ and supervisors’ placement experiences, data from the SPEF-R student review of professional practice placement survey, Student Evaluation of Placement questionnaire, and Clinical Educator Evaluation of Placement questionnaire will be summarised and reported descriptively. The 5-point Likert-style item responses on each questionnaire will be reported graphically. Differences in item ratings between groups of participants will be assessed using independent samples *t* tests*.* Additional thematic analyses will be carried out on written comments made on any of the instruments in conjunction with data obtained through focus group interviews. All qualitative data will be analysed inductively to address the question of perceived placement value and quality.

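### Confidence non-inferiority is judged by an unadjusted t test on change scores. Adjusting the post-placement score for baseline and site would be more precise at no cost, and a day-1 baseline comes after allocation.

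*Protocol article*

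**What the plan says.** Under Aims and research questions, the protocol article asks whether self-confidence after a simulated placement (SCP) is non-inferior to that after a traditional placement (TCP).

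- **Measure.** Under Student confidence: "Student confidence will be measured prior to placement and again at the end of placement". There are 41 self-report items, and "scores are summed for a total score ranging from 41 to 205" on each occasion.
- **Analysis.** Under Statistical analyses methods: "the difference between change scores on the confidence questionnaire between SCP and TCP groups will be assessed using an independent samples" *t* test. The same section adds: "Between-group analyses of mean total score differences on this questionnaire, both pre- and post-SCP and TCP, will be determined using independent samples" *t* tests, with paired tests within groups. None of these includes a covariate. The examination score, by contrast, is analysed by ANCOVA, and overall SPEF-R pass/fail by logistic regression with covariates.
- **Timing of the pre-score.** Table 2 allows two occasions: "Pre-placement briefing 1 week prior to placement" or "morning of 1^st^ day of placement".
- **Timing of allocation.** Under Recruitment, students are "invited to participate at the beginning of, or just prior to, the start of the semester in which the trial is to be implemented". Under Randomisation and allocation, each site's research assistant allocates students "utilising block randomisation once student enrolment in the unit of study is determined". Under Blinding, students are stated to be unblinded.

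**The concern.** Two separate matters arise.

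The first is precision. Subtracting the pre-score amounts to fixing its regression coefficient at 1, whatever the data show. When pre- and post-scores are imperfectly correlated, that coefficient is too large, and the comparison carries noise that a fitted coefficient would remove. In a non-inferiority comparison a wider interval lowers the chance of reaching a conclusion.

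The second is the status of the baseline. A pre-score taken on the first morning of placement comes after students know which placement they have. The measure is self-reported confidence about that placement, so expecting real or simulated clients could move it. If it does, the change score takes in the whole of that movement.

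**Working it through.** **The plan's own figure.** No sample size, SD, pre-post correlation or margin is given for confidence in the article. The only sample size is for the examination: 240 × [1 + (60 − 1) × 0.007] = 240 × 1.413 = 339, stated as 340, and 340/0.8 = 425. The upper end of the stated cluster-size range reproduces it. I use 340 analysed (170 per arm) only to illustrate scale.

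**Precision.** Assume equal pre and post variances (set to 1) and correlation ρ:

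- change score: variance 2(1 − ρ)
- ANCOVA of post on pre: variance 1 − ρ²
- ratio, ANCOVA to change: (1 − ρ²)/[2(1 − ρ)] = (1 + ρ)/2
- extra students for the change score: 2/(1 + ρ) − 1
- 95% CI half-width in SD units: 1.96 × √(variance × 2/170), ignoring clustering

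| ρ (assumed) | Variance ratio | Extra students | 340 by change score is worth, by ANCOVA | Half-width, change | Half-width, ANCOVA |
|---|---|---|---|---|---|
| 0.3 | 0.65 | 54% | 221 | 0.252 | 0.203 |
| 0.5 | 0.75 | 33% | 255 | 0.213 | 0.184 |
| 0.7 | 0.85 | 18% | 289 | 0.165 | 0.152 |
| 0.9 | 0.95 | 5% | 323 | 0.095 | 0.093 |

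Below ρ = 0.5 the change-score variance 2(1 − ρ) exceeds 1, so the change score is then less precise than the post-score alone.

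**Bias.** Suppose knowledge of allocation shifts the observed pre-score by δ in the SCP arm, with no effect on the post-score and no true difference. The expected arm difference is −δ for the change score, about −ρδ for ANCOVA, and 0 for the post-score alone. A simulation with 170 per arm, ρ = 0.5 and 4000 runs agrees:

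| Baseline shift | Change score | ANCOVA | Post-score alone |
|---|---|---|---|
| none | −0.001 (SE 0.108) | −0.003 (SE 0.094) | −0.004 (SE 0.110) |
| 0.2 SD | −0.20 | −0.10 | −0.002 |

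The 0.2 SD is an assumption; the documents give neither a size nor a direction. If expecting simulation lowered the SCP pre-score, SCP's gain would be overstated; if it raised the pre-score, SCP's gain would be understated.

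**Order of events.** On the first morning students are at their assigned placement, so knowledge of allocation is near certain. At the briefing a week earlier it is likely but not stated: the article gives no disclosure date, and the flow figures are not available here.

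**The case against.** The strongest reply is that the planned test is valid. With a baseline unaffected by allocation it is unbiased under randomisation, as the no-shift simulation shows, and chance baseline imbalance averages out. That stands, so the first matter is one of efficiency only.

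The size is also uncertain. The two measurements are about 4 to 12 days apart on a scale with a reported alpha of .96, so a high ρ is plausible. At ρ = 0.7 the half-widths differ by 0.165 − 0.152 = 0.013 SD, and at 0.9 hardly at all. That stands as well.

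Omitting site does not bias a comparison randomised within site, and subtraction already removes stable site differences in baseline confidence. Site adjustment is a modest addition.

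A reader might infer more from the text in three ways:

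- *The pre-score occasion differs between arms.* Table 2 lists both occasions for all students and reads most naturally as a choice made by site. The section on the TCP comparison group matches the arms on evaluation and on timing to within a week. A difference between sites alone would not bias the arm comparison.
- *The pre-score is used only by subtraction.* The plan also compares pre-scores and post-scores between groups. What is absent is any analysis of the post-score adjusted for the pre-score.
- *ANCOVA cures an affected baseline.* It reduces the bias to about ρ times the shift. The post-score comparison, which the plan already contains, avoids that bias.

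**Conclusion.** The point holds as a stated analysis choice that can be improved at no cost. Given equal pre and post variances and an assumed ρ of 0.3 to 0.9, the change-score *t* test needs about 5% to 54% more students than ANCOVA for the same precision. This loss does not by itself bias the result or produce a false claim of non-inferiority. With no confidence margin in the article, it cannot be tied to a changed conclusion.

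The baseline matter is conditional. It applies where the pre-questionnaire is completed on day 1, and possibly at the briefing, and only if knowing the allocation moves the score. The change score would then carry the whole shift. The documents do not support saying that such a shift occurred or that timing differed between arms. Confidence is a secondary outcome and the total of 425 is unaffected.

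**What to change.** Make the main confidence analysis an ANCOVA of post-placement score on pre-placement score, arm and site, and report the adjusted difference with its 95% confidence interval. Keep the between-group post-score comparison, adjusted for site, as a sensitivity analysis, because it does not use a baseline that allocation may have affected. Treat the between-group pre-score tests and the within-group paired tests as descriptive.

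This changes wording only and uses data already planned for collection. Trial status reports data collection complete at acceptance, so the questionnaire cannot be moved for this trial. In any future use, collect it on one common occasion before allocation is announced. The cost is that the interval then also covers some unit teaching, which both arms share.

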#### Economic evaluation

This economic evaluation is nested within the RCT and will be closely coordinated with the purpose, data collection and statistical analysis of the RCT. The method of economic analysis will be consistent with the research question, the study perspective, the study comparators and the target population as outlined above. The choice of method for economic analysis and the time horizon will depend on the study outcomes and the decision context.

If non-inferiority of SCP compared to TCP is established in the RCT, and SCP is shown to be less expensive than TCP, then a cost-minimisation analysis will be utilised. ‘Pathway analysis’ [37] will be used to clearly specify all activities in the SCP intervention and the TCP comparator (‘who teaches what to who, when, where and how often’). If the SCP is not inferior to the TCP, but it costs more, longer term benefits will be evaluated using cost-effectiveness ratios that have pedagogical and policy meaning; for example, time to complete the occupational therapy degree and participation in the workforce. A decision threshold value will be specified in terms of what constitutes ‘value for money’ with the chosen cost-effectiveness ratios.

### Ethical considerations

To support implementation, the design of the trial ensured there was no disincentive for students to participate. All university partners have adjusted curricular requirements for the particular unit of study in which the program will be situated so that all students can be allocated to either the SCP or TCP. In addition, data collection instruments are aligned to usual educational practices and ordinary performance assessment wherever possible. These adjustments have been considered by relevant curriculum authorities in each university (for example, an Academic Program Standing Committee) to ensure pedagogical integrity. Student assignment to the placement mode will be on the basis of random allocation, regardless of their decision to take part in the study. Eligible students will be provided with the opportunity to volunteer to participate in the study; the only difference between those participating and those not will be an agreement to allow data collected as part of the placement activity to be included in the trial. Student participants will not be incentivised or compensated, and there is no advantage to participating, or disadvantage to non-participation.

Clinical supervisors, for both SCP and TCP, and the educators who help to deliver the SCP program will also be invited to participate by contributing data. The SCP supervisors and educators will be paid for their time but will not be incentivised or additionally compensated for agreeing to contribute data to the study. The TCP supervisors undertake the student supervision role within their organisations in the usual way and receive no individual payment. Some organisations charge for student placement days, and where those agreements are in place, payments to organisations will be made in the usual way and this data collected as part of the economic component of the trial.

All participants (students, clinical supervisors, simulation facilitators) can elect to withdraw from participation in the study in part or in full, but still participate in the SCP or TCP activities. All data about and from students will be labelled with the student’s institutional student number but not their name. This ensures that the various items of data, which might be submitted separately and across a span of several weeks, can be matched to particular students, but that personal details, such as the students’ names, are kept separate from the data files.

Data security during and following completion of the study will be managed in the following ways. A local research assistant based at each of the eight partner institution sites will collect the data and upload it to the overall project management team via a secure cloud storage platform. That platform is only open to academics based at Australian universities. The data will be checked and verified by a national research assistant before it is added to a central database. Each local institution will retain the original data — paper-based instruments — as per each site’s ethics requirements. As each university’s data are added to the database, those data will be deleted from the cloud server; thus the cloud server is used as a data transmission mechanism rather than as a long-term data repository.

This RCT is deemed to entail a low level of ethical risk. Students already complete professional placement activities for occupational therapy and a range of other courses, and appropriate risk management processes are already in place at each partner university. An earlier version of the SCP program has been trialled at one university with no adverse outcomes. There is no expectation that the trial will need to stop prior to conclusion.

## Discussion

The use of simulation in health-related fields like occupational therapy is not unusual, but simulation typically relates to specific activities. For example, a simulated client might be hired for students to take turns to interview, or learning activities might be held in a mock kitchen. The simulation described here is innovative in that it encapsulates a 5-day block of integrated activities, designed and delivered in a manner that aims to emulate best-practice placement experiences. This simulation is designed to replicate, and potentially replace, a short-duration traditional placement experience.

A quality traditional placement experience would comprise a range of activities for the student to participate in, roles for the student to try out and a variety of clients and professionals for the student to engage with, all in a well-supported environment [8, 9]. Despite the best of intentions, not all traditional placements will, in reality, provide this experience for students [38]. Placements might occur at a quiet time in the organisation; the supervisor may need to undertake a range of desk-top tasks in which it is difficult to engage the students; or the student’s placement experience may, for many reasons, not be the priority for the supervisor or organisation at that particular time. One important advantage of the SCP is the consistency of the content and delivery experience, and therefore the likelihood that all students will be exposed to a particular set of experiences that can lead to achieving the desired learning outcomes.

A second innovation in this study is the inclusion of the economic evaluation. The comparison of student learning and student evaluations of their experience will speak to whether the SCP is as effective as the TCP. Economic evaluation will provide valuable information about the efficiency of offering block simulation as an integral (and integrated) component of allied health courses, to partially meet the professional practice experiences required for accreditation. The economic evaluation has been carefully designed to capture all costs of providing both the SCP and the TCP. These costs are not typically transparent, and this information will be very useful to the occupational therapy profession, universities and the health and human services sector who host placements. The cost collection will also help to address the question of affordability.

Feasibility of this RCT has been enhanced through initial consultation with all universities in Australia that offer occupational therapy education [39] and in partnering with six universities in the implementation of the trial. This partnering involved collaborative agreement about what SCP to implement, how to embed the SCP across varied curricula and which measures could be included as assessment tasks within chosen units of study. This collaborative partnering will support recruitment of sufficient student participants because the only difference between participating in the trial and not participating is the question of whether required assessment data will be forwarded for the study. These factors should result in a high consent rate. There is, however, a risk related to the need to procure sufficient TCP places. Anecdotal reports from each university indicate the increasing difficulty in securing TCP places.

The current trial includes design elements that will support dissemination and knowledge transfer across occupational therapy programs in Australia. Multisite trials that aim to exert high levels of control of the trial’s implementation would typically centrally train an SCP delivery team and data collection team and dispatch them to each university to implement the SCP program in parallel with that university’s TCP program. While this might provide evidence of the effect of a highly controlled intervention, the current study is pragmatic and will provide evidence of the effectiveness of a ‘real-world’ implementation because each university is responsible for implementing the RCT, in terms of delivering the program as well as collecting the data, at their own institution. Our protocols include provision of training via a training officer, the trial manager and one of the lead investigators visiting each site to prepare the local team to deliver the SCP, administer the RCT processes and collect the data. Detailed manuals and checklists have also been prepared and ongoing support put in place to assist each site. While a pragmatic approach entails some risk to the consistency of the implementation of the RCT, these risks are offset by both the practical advantages of having local teams implement the program and the increased rapidity of knowledge translation following trial completion through ongoing use of the materials and resources developed for the project — if the hypothesis that the two placement modes are equivalent is supported by the data. Local management also reflects how a placement program would be run at a university.

